#### Additional Covariates

Additional covariates for model adjustment will come from RAI-HC, DAD, NACRS, pharmaceutical, and claims records (eg, geriatric syndromes, medical diagnoses, and prescribed medications). We might also adjust for additional community care services (eg, in-home respite and home care).

### Statistical Analyses

#### Objective 1: Explore Patterns of Day Program Use

Using our day program cohort, we will conduct LCAs to determine the number of different day program use patterns, using the 4 variables described in the exposures section. LCAs are widely used to identify subgroups by clusters of characteristics (ie, parameters of day program use) [71]. In collaboration with our experts and guided by relevant literature, we will prespecify the expected number of classes. We will carry out LCAs separately in each province. We will run models with the prespecified number of classes, and with 1, 2, and 3 more and fewer classes than the number prespecified [71]. We will compare the fit between models, using bootstrap likelihood ratio tests [71], and select a final model that reflects the same number and types of classes in each province, balancing theoretical, conceptual, and statistical considerations. To assess temporal changes in the number of day program attendees within each use pattern, and differences between provinces, we will report and graphically plot the proportion (95% CI) of individuals within each latent class by quarter and province.

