### Setting and Sample

Our study settings are community-based continuing care systems. Each province provides access to a range of publicly funded community-based continuing care services, including adult day programs [55-63]. Each provincial health system determines and enacts access criteria and provides services (directly or via contracted providers) [55-63]. Day program eligibility is assessed in each province, using comparable processes, criteria, and assessments (ie, the Resident Assessment Instrument—Home Care [RAI-HC], a standardized, valid, reliable assessment tool [64]) [60,65,66]. To be eligible, attendees need to have not only some care dependency but also the ability to cope to some extent with activities of daily living, ambulate or transfer with no or minimal assistance, be continent or independent in managing continence products, exhibit no or easily manageable responsive behaviors, and either be alone for extended periods or have a caregiver who requires respite. Our study cohort will include all individuals aged 65 years or older with an initial RAI-HC assessment completed between January 1, 2012, and December 31, 2021. We will follow everyone until they move into a care home, are lost to follow-up (eg, because of death, moving out of province, loss of public insurance eligibility), or until December 31, 2024 (the end of the period covered by our data). That will allow for a care trajectory of at least 3 years (for those with an initial RAI-HC assessment in December 2021), enabling us to assess the number and characteristics of individuals with different day program use patterns, and compare them with those who were never exposed to a day program.

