### Study Variables

#### Exposure

Our exposure will be different patterns of day program use or nonuse, based on information from the provincial continuing care registries, documenting the dates a person starts or stops attending a day program, days of attendance, and the duration of each visit. Day program use patterns will be determined, using LCAs (see *Statistical Analyses* section) [71]. We will categorize three continuous variables as low, low-moderate, high-moderate, or high use, using sample distribution quartiles: (1) time between first RAI-HC assessment and first attendance of a day program; (2) average number of hours of day program attendance (ie, total number of hours spent in a day program divided by the number of times attended); and (3) total number of days a person attended a day program. LCAs will also include a categorical variable, indicating whether a person consistently attended a day program or whether there were longer periods (several weeks) of nonattendance. Nonuse will be defined as no day program exposure at any time during a person’s continuing care trajectory.

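### Use patterns are measured over potential follow-up that falls from 13 to 3 years with entry date, so objective 1's quarterly class plot can shift without any change in behaviour

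*Protocol article*

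**What the plan says.** All statements are in the protocol article.

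- **Setting and Sample.** Entry requires an "initial RAI-HC assessment completed between January 1, 2012, and December 31, 2021". On the end of observation: "We will follow everyone until they move into a care home, are lost to follow-up", or "until December 31, 2024 (the end of the period covered by our data"). The article comments on length of follow-up once: "That will allow for a care trajectory of at least 3 years (for those with an initial RAI-HC assessment in December 2021").
- **Exposure.** The latent class analysis has four inputs. Two are time from first RAI-HC to first attendance and the "total number of days a person attended a day program". The others are mean hours per visit and an indicator of interruptions lasting several weeks. The three continuous inputs are cut at quartiles of the sample. On nonuse: "Nonuse will be defined as no day program exposure at any time during a person"'s continuing care trajectory.
- **Objective 1 analysis.** The latent class analysis uses the day program cohort, that is, attendees. To assess temporal change and provincial differences, "we will report and graphically plot the proportion (95% CI) of individuals within each latent class by quarter and province". The section does not say whether quarter refers to entry, first attendance or calendar time of attendance.
- **Abstract and objective 2.** The abstract's objective 1 includes nonuse in the comparison over time. The objective 2 models interact year of assessment with use or nonuse class.

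**The concern.** A person who entered in early 2012 can be seen to start a day program up to 13 years later. A person who entered in December 2021 can be seen to start for only 3 years. Delay to first attendance cannot exceed the observed window, total days accumulate with it, and never attending becomes more likely as it shortens. A longer window also gives more chance of an interruption. Only mean hours per visit is free of this by construction.

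The definitions set no common window and no rate per time observed, and the results are then plotted against time. Class frequency over time is one of the two comparisons objective 1 makes, and the Discussion promises to tell health systems whether patterns have changed. With samples this large, narrow confidence intervals could surround a trend produced by the data cut-off.

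**Working it through.** **Plan's own figure.** December 31, 2021 to December 31, 2024 is 3.0 years, which reproduces the stated minimum. January 1, 2012 to December 31, 2024 is 13.0 years.

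**Ever-use with constant behaviour.** Let u be the yearly rate of starting a day program, m the yearly rate of leaving follow-up (care home, death, loss) and F the years from entry to the cut-off. Then

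P(ever use) = u/(u+m) × [1 − exp(−(u+m)F)].

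The article gives neither u nor m, so both are assumptions. Entrants are taken at mid-year: F = 12.5 for 2012 and F = 3.5 for 2021.

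| Assumption | 2012 entrants | 2021 entrants |
|---|---|---|
| u = 0.10, mean stay 4 years (m = 0.25) | 0.2857 × (1 − 0.0126) = 28.2% | 0.2857 × (1 − 0.2938) = 20.2% |
| u = 0.10, mean stay 3 years | 23.0% | 18.0% |
| u = 0.10, mean stay 6 years | 36.2% | 22.8% |
| u = 0.08, median stay 3 years (m = ln 2/3 = 0.231) | 25.2% | 17.1% |

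At the extremes F = 13 and F = 3, the last row gives 25.3% and 15.6%, a relative drop of 38%. Over median stays of 2-8 years and u of 0.03-0.15, the relative drop is 22% to 62%.

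**Longest-delay quartile, by entry year.** Write s = u + m and q for the pooled upper quartile of delay. Among attendees with window F, the share above q is

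[exp(−sq) − exp(−sF)] / [1 − exp(−sF)], or 0 if F ≤ q.

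With u = 0.08 and median stay 3 years, s = 0.311 and q = 3.48 years. Weighting numerator and denominator over F = 12-13 (2012 entrants) gives 32%; over F = 3-4 (2021 entrants) it gives 2%. The pooled cut lies above the whole window of those who entered in the second half of 2021. With u = 0.10 and mean stay 4 years, simulation gives 32% and 4%.

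**Other inputs, by entry year (simulation, 2012 versus 2021).** The most-days quartile is 27% versus 20% in one set of assumptions, and 26.2% versus 22.1% in another (27.6% versus 17.1% with longer attendance spells). Interrupted attendance is 19.4% versus 17.0%.

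**Same behaviour, other meanings of quarter.**

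- Calendar time of attendance: the longest-delay share of those attending is 0% in mid-2012, 29% in mid-2021 and 55% in mid-2024. The share of the cohort attending rises from 1.7% to 5.0%, then to about 5.5%.
- Quarter of first attendance: the longest-delay share is 0% in early 2012 and 77-100% in the last quarter of 2024. Entry stops on December 31, 2021, so anyone starting on or after October 1, 2024 has waited at least 2.75 years.

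**Common 36-month window.** Setting F = 3 for everyone gives 18.6% ever-use (u = 0.10, m = 0.25) in every entry year. For u = 0.08 and median stay 3 years, simulated ever-use is 15.5-15.8%, and both the longest-delay and most-days quartiles are 24-26%, in every entry year.

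**The case against.** A reader might infer that objective 1 will show falling use. The article does not support that, for two reasons. First, quarter is undefined. The stated purpose, change in the number of attendees within each pattern, fits calendar attendance at least as well as entry cohort, and on that reading the share attending rises and late starters become more common. Second, the plot covers attendees only. Nonuse is not one of its classes, so the ever-use figures describe the comparison in the abstract's objective and in objective 2, not this plot. Both points stand.

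It can also be said that no latent class model was fitted in the checks. They tabulate single inputs; only delay moves strongly, days move modestly and interruption little. That stands too: the shift in the classes themselves is unquantified.

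Finally, a journal article may leave window handling to shared protocols that are not shown, and objective 1 is exploratory with no trend test. This carries less weight. The article states definitions covering the whole trajectory, pooled cut-points and a plot meant to show change; following them as written produces the artefact. Its one remark on follow-up treats the 3-year minimum as sufficient.

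**Conclusion.** The concern holds in a limited form. The stated definitions can produce an artificial time shift in the use-pattern inputs with no change in behaviour, and a false shift in the delay input appears on each of the three readings of quarter examined. By quarter of entry, late starters decline strongly and high-volume attendees modestly; by quarter of first or calendar attendance, late starters increase. The same definition inflates nonuse among recent entrants wherever use and nonuse are compared over time.

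The sizes rest on assumed constant start and exit rates and uniform entry over 2012-2021. Ever-use fell from 2012 to 2021 entrants in every scenario tried, but its true size depends on exit rates the article does not give. The provincial comparison at a given time and the direction of any trend in the final classes are not settled by this check.

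**What to change.** For every time trend, derive the latent class indicators and use or nonuse from the first 36 months after the first RAI-HC, which every entrant has as potential follow-up. State that quarter means quarter of cohort entry, 2012-2021. Report classes from all available follow-up only as a secondary description, not as a time trend.

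This takes a change of wording and a date restriction in the shared provincial programs, with no new data. There are three costs. Use after 36 months leaves the trend figure, which matters because attendance can last years. The trend ends with 2021 entrants and says nothing about calendar change in 2022-2024. The 36-month classes must be labelled separately from any all-follow-up classes used in objectives 2 and 3, and kept consistent across the three provinces. Dividing total days by time observed would be a partial alternative: it addresses the days input but not delay to first attendance or nonuse.

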#### Objective 2: Compare Older Adults’ Characteristics by Day Program Use, Province, and Time

Using our full cohort of day program attendees and nonattendees, we will descriptively assess the distribution of sample characteristics over time and by province. In each province and quarter, we will report and plot graphically the proportion (95% CI) of individuals with each characteristic, stratified by day program use class versus nonuse. Using general estimating equations (GEEs) [83], we will assess whether the number of persons with each characteristic has changed over time and whether characteristics are associated with older adults’ day program use or nonuse pattern. We will run a separate GEE model for each characteristic within each province, with the respective characteristic as individual-level outcome. We will run binary logistic regressions for dichotomous variables (eg, sex) and ordinal regressions for categorical variables (eg, residential instability quintile). Models will account for repeated measures within individuals and include the independent variables year of assessment (to assess change in social determinants over time), use or nonuse class (to assess differences in social determinants by day program use), and an interaction between year and use or nonuse (to assess how social determinants differed between use and nonuse patterns by year). Using random-effects mixed regression models, we will pool provincial effects statistically. Other Pan-Canadian studies, such as the Canadian Network for Observational Drug Effect Studies [84], have successfully applied this approach and developed rigorous protocols to minimize bias and maximize consistency of regional analyses.

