#### Propensity Score–Matching Variables

To compare outcomes between day program attendees and nonattendees, we will use propensity score matching [78] (for details, see Statistical Analyses section). Propensity scores aim to ensure a similar distribution of baseline variables among treatment (day program attendees) and control (nonattendees)—akin to what random assignment aims to accomplish in randomized trials [78]. Since we lack evidence on differences between day program attendees and nonattendees, our objective 2 analyses will be key to informing the selection of the exact covariates that will form the propensity score. We will derive covariates for day program attendees from the RAI-HC day program eligibility assessment (index date). For each day program attendee, we will identify potential matches as nonattendees whose first RAI-HC assessment was completed within ±3 months of the attendee’s index date (ie, admission to long-term home care at about the same time). This RAI-HC assessment will provide the relevant covariates to enable propensity score matching with day program attendees as of their index date.

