Our first set of matching covariates will be RAI-HC variables used by health systems to determine day program eligibility [60,65,66]: physical functioning (ADLh Scale), cognition (CPS), behavioral symptoms (Aggressive Behavior Scale [79]), bladder or bowel continence (items I1, I3), availability of a caregiver (item G1e), and caregiver distress (items G2a-c). This will ensure that control participants are potentially eligible to a day program. Possible reasons for nonattendance include the lack of day program spaces, preference not to attend, inability to afford the required copayments, or not receiving a day program referral. Our experts assure us that the pool of potential matches far exceeds that of attendees, supporting the feasibility of this study and underscoring the lack of day program spaces. This approach excludes individuals whose care needs are either too low or too severe for day program eligibility, but it minimizes confounding by the matched variables and ensures comparable groups at baseline [80-82]. Finally, we will include a second set of matching covariates: health and social characteristics identified in objective 2 by which attendees and potentially eligible nonattendees differ and that overlap sufficiently between attendees and nonattendees (eg, age, sex, type or duration of publicly funded community care received before the matching index date, and deprivation indices).

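### Objective 2 describes users and nonusers over all their assessments, but choosing propensity score covariates needs a baseline comparison among people eligible for a day program

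*Protocol article*

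**What the plan says.** The Objective 2 analysis section starts from everyone: "Using our full cohort of day program attendees and nonattendees, we will descriptively assess the distribution of sample characteristics over time and by province". It then states: "We will run a separate GEE model for each characteristic within each province, with the respective characteristic as individual-level outcome". On the records and predictors it says: "Models will account for repeated measures within individuals and include the independent variables year of assessment", followed by use or nonuse class and a year-by-class interaction.

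The class is a label for the person, not for the assessment. In the Exposure section, "Nonuse will be defined as no day program exposure at any time during" the continuing care trajectory, and one of the variables that build the use classes is the "total number of days a person attended a day program". The Data Sources section says that the RAI-HC is repeated annually in long-term home care, so attendees will commonly have assessments after they start a program.

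The Propensity Score–Matching Variables section gives these analyses a second job: "our objective 2 analyses will be key to informing the selection of the exact covariates that will form the propensity score". The second set of matching covariates is to be "health and social characteristics identified in objective 2 by which attendees and potentially eligible nonattendees differ", subject to sufficient overlap. The same section fixes the first set by eligibility (physical function, cognition, behavior, continence, caregiver availability and distress) and takes attendees' covariate values from the eligibility assessment.

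**The concern.** Choosing matching covariates needs an answer to one question: at the index time, how do attendees differ from nonattendees who could have attended? The objective 2 models answer another: averaged over the assessments used, how do people who ever attended differ from all people who never did? The two diverge in two ways.

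- **Timing.** Attendees' assessments before and after first attendance carry the same class label. Objective 3 hypothesizes that attendance changes function, cognition, mental health and caregiver distress. The class term can therefore mix who attends with what happened during attendance.
- **Comparator.** The full cohort includes nonattendees whose needs are too low or too severe for a day program. The matching section wants the potentially eligible ones. This mismatch needs no assumption about any program effect.

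At stake are the reading of the objective 2 class term and the choice of the second set of matching covariates. A baseline difference that later closes or reverses could be overlooked. A difference that arises only during attendance could be reported as a feature of who attends.

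**Working it through.** The plan gives no figure on this point, so there is none to reproduce. The check is a reading of the sections, then an illustration.

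**Does the year interaction separate the periods?** Year is year of assessment. The Setting and Sample section admits first assessments from 2012 to 2021, so in any calendar year some attendees have not yet started and others are well into attendance. Calendar year does not index time from first attendance.

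**How much can pooling hide?** Suppose each attendee has 1 assessment before and 2 after starting, and nonattendees stay at 25% (all assumed). Then

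pooled gap = (1 × gap at entry + 2 × gap after) / 3.

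| Attendees, entry then after | Calculation (points) | Pooled gap | Gap at entry |
|---|---|---|---|
| 25% then 20% | (0 − 5 − 5)/3 | −3.3 | 0 |
| 30% then 23% | (5 − 2 − 2)/3 | 0.3 | 5 |
| 35% then 22% | (10 − 3 − 3)/3 | 1.3 | 10 |
| 30% then 28% | (5 + 3 + 3)/3 | 3.7 | 5 |

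Exact cancellation requires gap after = −(gap at entry)/2, a reversal of sign. If the gap merely closes to zero, one third of it remains.

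**What would the tests flag?** Assumed inputs: 2,000 attendees, 6,000 nonattendees, latent within-person correlation 0.4, 5% level. The class-only column compares person means over 2,000 replicates. The joint column tests class and class-by-calendar-year together, with entry spread over 2012 to 2021. Its ranges span two separate simulations, one of them with 150 runs, where the Monte Carlo standard error at 14% is √(0.14 × 0.86/150) = 2.8 points.

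| Scenario | Class only | Class + class-by-year | Index assessment only |
|---|---|---|---|
| 25% then 20% | 99% | 99% to 100% | 4% to 5% |
| 30% then 23% | 7% | 14% to 16% | 99% to 100% |
| 35% then 22% | 37% | 67% | 100% |
| 30% then 28% | not run | 99% | as row 2 (same entry gap) |

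With no difference at entry and no change afterwards, the pooled, joint and index tests each flagged about 5%.

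**A second set-up.** With 2,000 people per group, 4 annual assessments and attendance after the first, a logistic GEE on all assessments was compared with a logistic model on the first assessment only (60 runs per scenario). With no baseline difference and an attendance odds ratio of 0.7, the class odds ratio was 0.82 and was flagged in 100% of runs; the first assessment alone gave 1.00 and 5%. With a baseline conditional odds ratio of 1.3 offset by the same attendance effect, the class odds ratio was 0.98, flagged in 5%; the first assessment alone gave 1.20 and 78%.

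**Which covariates are exposed?** Of the characteristics that the protocol lists for objective 2, those that attendance could most plausibly change (ADLh, CPS, caregiver availability and burden) are in the fixed first set. Age and sex cannot be changed by attendance, and area deprivation hardly. The service-use example named for the second set is care received before the index date. What remains is other changeable health or social characteristics that the plan does not name.

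**The case against.** The strongest reply is that objective 2 is descriptive and does not claim to model who starts attending. Comparing the characteristics of users and nonusers by year is a legitimate aim, and all assessments may serve it. That stands.

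Second, the model contains a year-by-class interaction, and proportions are also reported by quarter and class. In the second set-up, a joint test with an interaction flagged the masked difference in 82% of runs. That interaction used time since first assessment, however. With calendar year and staggered entry, the joint test flagged the 30%-then-23% case in only 14% to 16%. The interaction helps a little but does not repair the comparison.

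Third, the plan says that objective 2 informs covariate selection. It sets no P value rule, does not say that the class term decides, and already names eligible nonattendees as the comparator. Covariates that differ at P ≤ .15 in the bivariate analyses can also enter the objective 3 outcome models. So a masked characteristic would not necessarily be lost. This stands in part: the objective 2 section describes no baseline, eligible-only analysis, and the bivariate comparisons are made in every year, so they can also draw on assessments after attendance began.

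Fourth, the inclusion of assessments after attendance is inferred from the full cohort, the repeated measures and the absence of any restriction. The article does not say it outright, and a fuller plan might restrict the records.

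A reader might infer that values measured after attendance enter the propensity score, or that objective 3 is biased throughout. The documents do not support either. Score values come from the index assessment, and the eligibility variables are matched whatever objective 2 shows. A characteristic flagged wrongly would merely be matched although already balanced at index, which does little harm.

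**Conclusion.** The concern holds in a limited form. As written, the objective 2 models can describe users and nonusers by year, but their class term does not show who attends. They are not the baseline, eligible-only comparison that the matching section relies on.

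For objective 2, this affects how the class term is interpreted for disability, cognition and caregiver burden. For objective 3, the risk is limited to changeable health or social characteristics outside the first matching set. There, serious masking arises only if the gap between attendees and nonattendees closes or reverses after attendance starts; a milder change (30% to 28%, against 25%) was still detected in 99% of runs.

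The detection rates rest on assumed prevalences, correlation, group sizes and numbers of assessments. They show the mechanism and do not predict this cohort. The comparator mismatch depends on none of them.

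**What to change.** State that the second set of propensity score covariates will be chosen from one assessment per person: the eligibility (index) RAI-HC for attendees, and the RAI-HC in the matching window for nonattendees who meet the eligibility-related RAI-HC criteria. Keep the repeated-measures GEE as a separate description of users and nonusers over time. Add an indicator for assessments made after first attendance, and say that the class term is not to be read as who attends.

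The cost is some wording and one additional run of the same models in each province, on assessments that the matching already requires. The selection analysis has fewer records per person, which is negligible with the more than 20,000 attendees per year that the protocol expects.
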